#### Assessment of intervention fidelity

PASS sessions will be audio recorded to enable our team to examine intervention content fidelity. The PASS treatment manual includes two standard sessions (sessions one and two) that are always presented and a variable number of additional sessions (sessions 3 +) that can be selected depending on presenting concern and family need or preference. Checklists reflecting session components will be used to assess content fidelity. Up to four sessions will be selected for content coding for each participant in the PASS condition. Sessions one and two will always be coded. One randomly selected session from sessions 3–5 and another from sessions 6 + will be selected for coding. Independent coders who have previous training in psychosocial treatment of ADHD will code all selected tapes and 25% of tapes will be double-coded to establish inter-rater reliability. An intraclass correlation coefficient (ICC) of at least 0.6 will indicate acceptable agreement [37].

The Community Health Partner will complete a survey after each encounter with a caregiver that provides information on topics discussed, barriers, stressors, strategies to address barriers and stressors, caregiver perceptions of care, resources, and the support process included in the call. To monitor Community Health Partner process fidelity, we will use a self-evaluation checklist completed by Community Health Partners after contact with a family. Process items include establishing trust, listening attentively, and re-directing tangential comments [38].

#### Measures of outcomes – examined for objective 1

Outcomes are differentiated into primary versus secondary and informant providing data (parent, teacher, child self-report). Two parent-report measures (ratings of homework performance and behavior compliance) have been identified as primary because these are a major focus of the PASS intervention. Teacher-report measures are secondary because of challenges obtaining these data due in large part to the burden placed on schools. Child self-report measures are secondary because some children, especially those under the age of 8, may have difficulty understanding and responding to these measures.

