### Sample size

Based on prior research [26, 28, 35], the magnitude of the effect size reflecting the degree of change in response to PASS vs TAU for service use and child outcomes (Objective 1) and care processes (Objective 2) is expected to be the 0.35 to 0.60 SD range. Based on prior research using a similar behavioral intervention [41], we assumed a standard deviation for a single observation = 0.50 and an autocorrelation = 0.3. Projecting an enrollment of 300 participants (150 per condition), and given an expected 20% attrition rate, we expect 240 participants will provide parent-report and child self-report data at baseline and at least one other data collection point. Using statistical methods described below, analytic models will achieve 85% power to detect an effect size as small as 0.30 SD. Given the challenges of collecting data from teachers related to the COVID-19 pandemic, the number of evaluable cases will be well below 240 (estimated to be 100). As such, analyses of teacher-report data will be exploratory. In addition, analyses of mediation (Objective 3) and subgroup effects (Objective 4) will be exploratory.

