If families participate in the study, they will be randomly assigned to PASS or TAU. With family consent, a member of the research team will contact the child’s teacher. We will use procedures successfully employed in previous studies [41] to obtain teacher buy-in: (a) an email will be sent to inform the principal that a parent or guardian has given permission for data collection from a student’s teacher, and the principal will be encouraged to contact the team if there are any concerns, (b) a member of the team will contact the teacher via phone and email, (c) teachers will be provided a “Teacher Information Sheet” that includes details of the study and a copy of the signed consent form giving parent permission to obtain data from the teacher, and (d) the study team will ask the teacher to complete baseline measures and a brief demographic form. Similar procedures will be used for data collection at other assessment points. See Fig. 2 for an illustration of participant flow through the study.

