#### Data collection and management

Data collection strategies were designed in partnership with caregiver, educator, and clinician partners. The strategies will be reviewed and modified throughout the study to maximize participant engagement in data collection and minimize missing data. Baseline data will be collected from parents and children at the time of consent, and baseline data will be collected from teachers shortly thereafter. Mid-treatment data (specifically the ODD items from the Vanderbilt scale and the Inattention/Task Avoidance items of the Homework Problem Checklist) will be collected from parents approximately 8 weeks after baseline, and post-treatment data will be collected from parents and teachers 16 weeks after baseline. Follow-up data will be collected from parents and teachers 32 weeks after baseline. Study data will be collected and managed using REDCap tools hosted at our institution [61, 62].

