Most of the outcome domains examined under Objective 1 include two measures. For example, there are two primary outcome measures – parent report of homework problems and parent report of behavior problems. In addition, ADHD symptoms will be assessed by parent report of inattention and hyperactivity-impulsivity symptoms. Because each domain generally will be assessed using two measures, tests of significance within each outcome domain will be examined using an adjusted *p* value. We have elected to use the conservative Bonferroni approach, and therefore will use a p value of 0.05/2 = 0.025. As indicated, analyses of measures completed by teachers will be underpowered. We will conduct these analyses using a* p* value of 0.05, but the primary focus will be on evaluating the magnitude of the effect size.

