#### Determination of intervention effect sizes

To estimate the magnitude of the intervention effect, we will compute Cohen’s *d*. This statistic will be calculated as the ratio of between-group differences in changes in expected values over time divided by the standard deviation of the combined, unadjusted baseline scores for each outcome measure.

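### Teacher effects are defined as change from baseline on a schedule not tied to the school year, so week-32 contrasts may span two raters and lose precision

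*Protocol article*

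**What the plan says.** Under Data collection and management, the teacher schedule is set purely in weeks. After parents and children give baseline data at consent, "baseline data will be collected from teachers shortly thereafter". Then "post-treatment data will be collected from parents and teachers 16 weeks after baseline", and "Follow-up data will be collected from parents and teachers 32 weeks after baseline". School terms are not mentioned. The Recruitment section describes clinician referral, regular reports from the health record and self-referral by QR code, with no enrolment season. On later teacher contact it says only "Similar procedures will be used for data collection at other assessment points".

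The Objective 1 analysis treats baseline as one of the repeated time points, with treatment, time and their interaction. It reports the between-group difference in estimated mean change. Determination of intervention effect sizes defines Cohen's d as the "ratio of between-group differences in changes in expected values over time divided by the standard deviation of the combined, unadjusted baseline scores". For teacher measures, the Objective 1 plan puts the size of the effect ahead of the significance test.

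The status of these outcomes is stated openly. Under Measures of outcomes, "Teacher-report measures are secondary because of challenges obtaining these data". Under Sample size, about 100 evaluable cases are expected and "analyses of teacher-report data will be exploratory".

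**The concern.** A 32-week interval fits inside one school year only for children whose baseline falls near its start. For others, the week-32 date falls in the summer recess or in the next school year, when the child will usually have a new teacher. The change score then subtracts one adult's rating from another's.

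Two things are at stake. The first is precision: two raters usually agree less than one rater does with herself, and a change score handles low correlation badly. The second is meaning. The PASS section describes a problem-solving partnership between caregivers and teachers, so the baseline-year teacher takes part in the intervention, while a next-year teacher ordinarily has not. The week-32 estimate would pool the effect seen by a participating teacher with carry-over to a new one, in proportions set by the enrolment calendar. This is hardest to interpret for the teacher form of the Parent-Teacher Involvement Questionnaire. That form rates one parent-teacher relationship, so change across two teachers compares two relationships.

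**Working it through.** The article gives no school-year length, enrolment calendar or share of children changing teacher, so there is no stated figure to reproduce. The shares below rest on assumptions.

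**1. Who can rate at week 32.** From the article: teacher ratings at 0, 16 and 32 weeks. Assumed: a 41-week school year, an 11-week recess, and baselines uniform over 52 weeks. Let t be the baseline week, counted from the start of the school year.

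- Same school year: t + 32 < 41, so t < 9. Share 9/52 = 17%.
- Week-32 date in recess: 9 ≤ t < 20, which is 11 weeks.
- Next school year: 20 ≤ t < 41. Share 21/52 = 40%.
- Baseline in recess: 41 ≤ t < 52, which is 11 weeks.
- Either date in recess: (11 + 11)/52 = 42%.

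Of the 9 + 21 = 30 baseline weeks that give a term-time pair, 21/30 = 70% span two school years. At week 16 the same-year share is 25/52 = 48%, and 5 of 30 term-time pairs (17%) span two years. The issue is therefore mainly one of week 32.

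**2. Sensitivity.** With a recess of 10 to 12 weeks, the same-year share is 10/52 to 8/52 (19% to 15%) and the next-year share 22/52 to 20/52 (42% to 38%). The enrolment pattern matters far more. The share whose week-32 date falls after the baseline school year ends is 1 − (L − 32)/M, where L is school-year length and M the width of the baseline window, both in weeks:

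| Enrolment pattern | Crossing by week 32 |
|---|---|
| Even over the school year, L = 44 to 36 | 73% to 89% |
| Even over 52 weeks, L = 44 to 36 (recess baselines counted) | 77% to 92% |
| First 26 weeks only, L = 40 | 69% |
| First 16 weeks only, L = 40 | 50% |
| First 12 weeks only, L = 40 | 33% |
| First 8 weeks only, L = 40 | 0% |

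Crossing is not the same as a changed rater. For L = 40 with even enrolment over the school year, the 80% splits into 12/40 = 30% landing in recess and 20/40 = 50% in the next school year.

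**3. Precision.** Take 100 evaluable cases (Sample size) as 50 per arm, with unit SD and baseline-to-follow-up correlation ρ.

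- Change: SE(d) = √[2(1 − ρ) × 2/50].
- Baseline-adjusted: SE(d) = √[(1 − ρ²) × 2/50].
- Variance ratio, change to adjusted: 2/(1 + ρ).

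| ρ | SE, change | SE, adjusted | Variance ratio |
|---|---|---|---|
| 0.3 | √0.056 = 0.24 | √0.0364 = 0.19 | 1.54 |
| 0.1 | √0.072 = 0.27 | √0.0396 = 0.20 | 1.82 |

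The article's planning autocorrelation is 0.3; 0.1 is an assumed value for two different teachers. At ρ = 0.1 the 95% half-width for d is 1.96 × 0.268 = 0.53 on change and 1.96 × 0.199 = 0.39 adjusted. The article expects effects of 0.35 to 0.60 SD.

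**The case against.** The strongest reply has five parts.

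- **No same-teacher rule exists to be broken.** The difference at week 32 as rated by the child's current teacher is a legitimate target for a pragmatic trial. This stands.
- **Randomisation protects the contrast.** Children are individually randomised within practice, so calendar timing is balanced between arms in expectation. A reader might infer that changing raters biases the week-32 comparison. It does not; it adds noise and mixes two kinds of rating.
- **The frequency is unknown.** A reader might infer that a same-teacher rating is impossible for about four in five children. That needs a school-year length and an enrolment pattern that the article does not give. It also counts recess dates as changed raters, although these would give a missing rating or one from the former teacher. Under the even-enrolment model, about two in five children have a next-year rater.
- **Change versus adjustment is a general efficiency point.** True: at the planning correlation of 0.3, change is already the noisier choice. What is particular here is that the penalty grows as agreement falls. The unstructured covariance will report that noise honestly, but with arm-specific baseline means it does not remove it.
- **The article is condensed.** Which teacher is contacted after a grade change may well stand in the full protocol. Its absence here is not the finding. The finding is the change-based effect that the article does fix, combined with its week-based schedule.

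**Conclusion.** The point holds in a limited form. The article fixes a teacher schedule and an effect measure that fit poorly together at week 32. Under even enrolment and a 41-week school year, about 40% of children would be rated at week 32 by a next-year teacher and about 17% could be rated by the same current teacher. These shares depend strongly on the unstated enrolment calendar, and confining enrolment to early autumn could make crossing negligible.

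The cost is precision and interpretability, not bias: an SE for d of 0.24 to 0.27 on change against 0.19 to 0.20 adjusted, at assumed correlations of 0.3 to 0.1 and 50 per arm. Both primary outcomes are parent-reported and are not affected by a change of teacher. The teacher analyses are secondary, exploratory and acknowledged as underpowered. Because their stated product is an effect size, the loss is still worth avoiding.

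**What to change.** In the Objective 1 and effect-size sections, keep the teacher estimates at weeks 16 and 32 in all randomised children. Estimate them as arm differences adjusted for the baseline teacher rating, or from the repeated-measures model with arm means constrained equal at baseline, and not as differences in change. Divide by the baseline SD as now planned. Apply the same to the teacher-rated parent-teacher relationship.

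Record the teacher and the school year with each rating. Add a supplementary week-32 analysis split by whether the scheduled baseline and week-32 dates fall in the same or the next school year, with children who have a recess date described separately. Define the split from the consent date and the school calendar. Both are settled before randomisation, so the comparison within each group stays randomised.

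Do not replace the all-randomised analysis with a same-year subset. By the model above, a same-year subset would keep only about 48% of children at week 16, and making week 16 the main result would demote a time point named in the first objective.

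The cost is a data field, if none exists already, and revised analysis wording. The split will give small groups in an already exploratory analysis. One weakness remains: the teacher baseline is taken shortly after consent, allocation is revealed at enrolment, and teachers are not blinded, so that rating may reflect knowledge of the arm. The change score has the same weakness.

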#### Plans to address missing data

Numerous strategies will be applied to minimize missing data, including persistent efforts to contact parents and teachers, disseminating study newsletters on a periodic basis, and motivational interviewing strategies. Alternative methods of imputation, including the maximum likelihood method [63] and multiple imputation method will be considered. In addition, we will check whether patterns of missingness differ between the PASS and TAU groups to determine whether the amount of missingness is associated with a particular group.

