#### Treatment as usual (TAU)

The control condition (TAU) includes access to existing integrated behavioral health service in primary care. Services provided to families in primary care during the 16-week intervention period are highly variable. The lag time from referral to first appointment and the availability of follow-up appointments after first visit vary markedly across practices. TAU does not include support from a Community Health Partner. Both conditions will include ongoing pediatric health care informed by AAP guidelines for managing ADHD [19] and facilitated by electronic practice supports, which have been successfully incorporated into the EHR to guide PCPs in implementing ADHD guidelines. Families assigned to TAU may be referred for community-based behavioral health services during the study period.

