## A priori plans for data analysis for each objective

### Objective 1 (Evaluate differences between PASS and TAU in improving service utilization and child health outcomes)

To evaluate changes in service utilization, we will examine between-group changes in the proportion of children receiving mental health services (i.e., outpatient mental health therapy, school mental health services and special education services, and psychotropic medication) from pre-treatment to post-treatment to follow-up using the McNemar test. To evaluate the effect of intervention on child outcomes, a mixed effects model with repeated measures (MMRM) will be the general analytical approach employed. The model will examine intervention effects across four time points (baseline, mid-treatment [parent report of homework performance and behavior compliance only], post-treatment, follow-up). Data for all participants randomized to treatment condition will be included in the analytic model, consistent with an intent-to-treat (ITT) approach. Mixed effects models will estimate within-subject effects by time and between-treatment effects, as well as the interaction of time by treatment. A significant time by treatment interaction will indicate that one treatment is superior to the other. MMRM will include the fixed categorical effects of treatment, time, randomization stratification factor (medication status and primary care practice), and treatment-by-time interaction as well as covariates as indicated. Within-participant error variance–covariance will be assumed to be an unstructured matrix. Point estimates and confidence intervals for the mean change in outcomes for each treatment group as well as the difference in the estimated mean change between groups will be calculated.

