### Objective 2 (Evaluate differences between PASS and TAU in changing parenting practices, improving family empowerment in seeking services, and improving caregiver perceptions of team-based care)

MMRM using an ITT approach will be the general analytical approach for testing Objective 2. The analytic model for examining Objective 2 will examine intervention effects across three time points (baseline, post-treatment, follow-up). We will test for significance using a *p* value of 0.025 to be consistent across analyses.

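### The stated missing-data check looks at the amount missing by arm and would miss equal but differently selective loss; for continuous secondary and Objective 2 outcomes the week-8 ratings that could help are outside the models

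*Protocol article*

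**What the plan says.** Protocol article, Plans to address missing data: for imputation, methods "including the maximum likelihood method [63] and multiple imputation method will be considered". The one diagnostic compares missingness in PASS with missingness in TAU, and its stated aim is "to determine whether the amount of missingness is associated with a particular group". The sentence opens on patterns, and this purpose clause then narrows the aim to amount by arm. The section states no comparison of children with and without later data on any score.

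Data collection and management: at mid-treatment, about week 8, parents in both arms give two sets of ratings, "specifically the ODD items from the Vanderbilt scale and the Inattention/Task Avoidance items of the Homework Problem Checklist".

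Analysis plan, Objective 1: the week-8 time point is limited to "mid-treatment [parent report of homework performance and behavior compliance only", that is, to the two primary outcomes. Other continuous Objective 1 outcomes have no week-8 value. Objective 2: the model "will examine intervention effects across three time points (baseline, post-treatment, follow-up").

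Treatment as usual: "TAU does not include support from a Community Health Partner". In PASS that partner phones families to promote attendance and resolve barriers.

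**The concern.** Equal amounts of missing data do not show that the missing children are alike. A between-arm contrast is distorted when the two arms lose different kinds of children, and this can happen at identical rates. It is plausible here: allocation is open, parents supply most of the outcomes, and only PASS families have contact with a Community Health Partner.

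For each primary outcome, the mixed model conditions on that outcome's own week-8 value, so loss that depends on it is covered. For a continuous secondary or Objective 2 measure, a child who leaves after week 8 contributes only a baseline score, plus whatever baseline covariates the model holds. If leaving depends on week-8 behavior, the data are then not missing at random given what is modelled, although the relevant ratings have been collected. The parent- and child-report comparisons concerned are mostly to be tested at 0.025, and a clean result on the stated check would give unwarranted reassurance about them.

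**Working it through.** **The plan's own figures.** Sample size section: 300 × (1 − 0.20) = 240, or 120 per arm. Stated power is 85% at 0.30 SD. With autocorrelation 0.3 (AR(1)), the mean of three measures has variance factor [3 + 2(2 × 0.3 + 0.09)]/9 = 0.487. The SE is √0.487 × √(2/120) = 0.090 SD, and 0.30/0.090 = 3.33. At two-sided 0.025 (z = 2.24), power is Φ(3.33 − 2.24) ≈ 0.86. The stated figure is reproduced, and this point does not change it.

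**Can the check see the problem?** In a simulation of 3,000 trials (150 per arm, 20% lost in each arm), a 5% chi-square test of the amount missing by arm flagged 4% to 6% of trials in every scenario, whether the contrast was biased or not. That is simply its false-positive rate.

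**How large is the bias?** The documents give no correlation between week-8 ratings and later secondary scores, and no rate or pattern of loss after week 8. The following are assumptions:
- Loss after week 8 is at the same rate m in both arms, unrelated to behavior in PASS. In TAU it is logistic in week-8 ODD with slope b = 0.5 to 1.0 per SD.
- Week-8 ODD correlates r = 0.3 to 0.5 with the week-16 outcome.
- The baseline outcome correlates 0.3 with the week-16 outcome (the protocol's autocorrelation) and 0.2 with week-8 ODD.

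For a standard normal week-8 score, its mean among retained TAU children falls by

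shift = b × E[p(1 − p)] / (1 − m),

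where p is the individual probability of loss and the intercept is set so that the mean of p is m. What passes into the contrast after baseline adjustment is about

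bias = (r − 0.2 × 0.3) × shift, that is, 0.24 to 0.44 times the shift.

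| Lost after week 8 (m) | Shift, b = 0.5 | Shift, b = 1.0 | Bias, smallest | Bias, largest |
|---|---|---|---|---|
| 5% | 0.025 | 0.047 | 0.24 × 0.025 = 0.006 | 0.44 × 0.047 = 0.021 |
| 10% | 0.049 | 0.091 | 0.24 × 0.049 = 0.012 | 0.44 × 0.091 = 0.040 |
| 20% | 0.096 | 0.173 | 0.24 × 0.096 = 0.023 | 0.44 × 0.173 = 0.076 |

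Simulation with 2 million children per arm agrees at 20%: 0.022 to 0.077 SD. If the baseline outcome is taken as unrelated to week-8 ODD, the multiplier is 0.3 to 0.5 and the largest values become 0.024, 0.045 and 0.087 SD.

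**Other cases.** If selection is the same in both arms, the bias in the contrast is 0.00 SD. A deliberately steep case (slope 1.5 per SD, r = 0.3 to 0.6, all 20% lost after week 8) gives 0.05 to 0.12 SD when one arm is selective and 0.10 to 0.24 SD when the arms select in opposite directions. With week-8 ODD in the model, the bias is 0.00 in every simulated case. This is so by construction, because loss was generated from that score alone.

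**Effect on a test.** The SE of a baseline-adjusted week-16 contrast is about √(0.91 × 2/120) = 0.12 SD. A bias of 0.02 to 0.08 SD raises rejection of a true null at 0.025 to roughly 3% to 6%.

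**The case against.** The strongest reply is that imputation details belong in an analysis plan that is not shown. The article leaves multiple imputation open and nothing in it excludes week-8 auxiliary variables. That stands for the imputation model. It does not answer the purpose given for the diagnostic or the time points given for the models, which are written here.

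Several stronger readings are tempting and are not supported:
- A reader might infer that the week-8 ratings go unused. They are in the mixed model for both primary outcomes.
- A reader might infer that only a count by arm is intended. The sentence begins with patterns, which is wider, although its purpose clause names the amount.
- A reader might apply the full 20% attrition to loss after week 8. The Sample size section counts 240 children with baseline and at least one later data point, so the 20% appear to be children with no post-baseline data. Week-8 ratings cannot recover them.
- A reader might infer that equal selective loss always biases the contrast. It does so only if selection differs by arm. The Community Health Partner's calls concern PASS attendance and strategies, not study assessments, and the retention efforts are not limited to one arm. Differing selection is therefore plausible but not shown.
- A reader might take the simulated 0.00 as proof that adding week 8 restores missing at random. Loss driven by unobserved week-16 scores, or by traits unrelated to ODD and homework, would remain.
- A reader might infer that stress or financial strain are shut out of the models. The Objective 1 model allows covariates as indicated.

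**Conclusion.** The point holds in limited form. The one stated check is aimed at the amount missing by arm and cannot detect loss that is equal in amount but selective in different ways. For the continuous secondary parent- and child-report outcomes and the Objective 2 measures, the stated models do not handle loss after week 8 that depends on week-8 behavior.

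If only TAU is selective, the bias is about 0.01 to 0.025 SD with 5% lost after week 8, 0.01 to 0.05 SD with 10%, and 0.02 to 0.09 SD with 20% (0.02 to 0.08 SD when the baseline outcome correlates 0.2 with week-8 ODD). The smallest planned effect is 0.30 SD. These figures rest on assumed slopes of 0.5 to 1.0, assumed correlations of 0.3 to 0.5, and an assumed rate of loss; the 20% row is probably high for this trial. The primary outcomes and the stated 85% power are unaffected. Minor priority.

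**What to change.** 1. Extend the check. Model missingness at week 16 and at week 32 on arm, baseline outcome, and week-8 ODD and homework scores, with arm-by-score interactions. The interactions are the terms that reveal selection differing by arm. Report them beside the amount by arm.
2. For the continuous secondary and Objective 2 outcomes, include the week-8 ODD and homework scores as auxiliary variables in the multiple imputation already under consideration, run separately by arm. Alternatively, enter them as extra responses in a joint mixed model.
3. Say what this does not cover: children without a week-8 rating, and loss driven by unobserved scores.

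The cost is some extra programming and a few lines of plan wording. No new data or family contacts are needed.
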